### Blinding

The study is not blinded. Decisions regarding ongoing care, for example, the need for intubation and mechanical ventilation are made by the clinical team alone according to the unit’s guidelines.

### Intervention

At delivery, eligible infants are randomised either to receive five inflations each of 2–3 s duration as per the current UK Neonatal Life Support guidelines [2] or a 15-s sustained inflation (Fig. 1). Resuscitation is performed using a t-piece device (Neopuff Infant Resuscitator, Fisher & Paykel Healthcare, Auckland, New Zealand). Both the sustained inflation and the five 2–3 s inflations are performed using a peak inspiratory pressure of 25 cmH_2_O and PEEP of 5 cm H_2_O as per unit guidelines. As per unit guidelines, PEEP of 5 cmH_2_O is provided between inflations and between sets of inflations. Either the sustained inflations or the five inflation breaths may be repeated once and, if the baby is initially resuscitated by facemask and subsequently intubated, the sustained inflations or five 2–3 s inflations as per randomisation may be repeated twice if necessary. All trainees are trained to deliver the sustained inflation on a mannequin and using the respiratory function monitoring equipment.

**Fig. 1 Fig1:**
[figure not shown]
Trial *flowchart* (Protocol v3, 31/8/16)

The resuscitation is recorded using a respiratory function monitor (NM3 respiratory profile monitor; Philips Respironics, CT, USA). The monitor records flow, pressure, ETCO_2_ and tidal volume from a combined flow and carbon dioxide sensor that is placed between the Neopuff device and the endotracheal tube or facemask. Heart rate and oxygen saturations are recorded on the same device from a saturation probe applied to the right wrist (Masimo SET; Masimo Corporation, Irvine, CA, USA). Data are displayed and recorded on a personal computer running customised Spectra software (3.0.1.4) (Grove Medical, London, UK).

### Primary outcome measure

The primary outcome measure is the minute volume in the first minute of ventilation

### Secondary outcomes

The secondary outcome measures are the time to the first active inflation and the ETCO_2_ level in the first minute of resuscitation.

### Sample size

We have previously demonstrated that active compared to passive inflations during resuscitation at least double expiratory tidal volumes and ETCO_2_ levels [3]. During resuscitation with inflations of 1–3 s in duration, all infants had an active inflation by 50 s, but the active inflation occurred earlier in those who received longer rather than shorter inflations. The standard deviation of the minute volume was 71 mL/min/kg, which was 25% of the maximum minute volume achieved [3]. We, therefore, postulate that over the first minute of resuscitation the total expiratory tidal volume (minute volume) will be 25% higher in the sustained inflation group. Randomisation of 40 infants allows us to detect a difference of 71 mL/min/kg between the two groups with 90% power at the 5% significance level.

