## Background

Seventy-five percent of infants born at < 34 weeks of gestational age require resuscitation including positive pressure ventilation and/or endotracheal intubation at delivery [1]. Current UK guidelines recommend initial resuscitation using five inflations of 2–3 s duration with peak inflation pressures of 20–25 cmH_2_O [2]. It has been shown, however, that despite resuscitation training, clinicians in both simulated and real resuscitation scenarios do not deliver the recommended duration of the inflations [3, 4]. This, combined with leaks around the facemask often as large as 50% or greater, contributes to low expired tidal volumes during resuscitation [5]. Indeed, during resuscitation by facemask or endotracheal tube, tidal volumes and end tidal carbon dioxide (ETCO_2_) levels remained low until a respiratory effort was made coinciding with a mechanical inflation (an active inflation) [3, 6]. Analysis of data collected during the resuscitation of infants born at < 34 weeks of gestational age who received inflations of 1–3 s in duration demonstrated that active inflations occurred sooner with longer inflation times [7].

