## Methods

This is a non-blinded, randomised superiority trial. Infants are allocated to parallel groups in a 1:1 ratio.

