### Exclusion criteria

Major congenital abnormalitiesRefusal of consent for the data to be analysed (see later).

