### Enrolment

Infants will be enrolled in the study by the clinical team attending the delivery. Infants will be deemed to be enrolled if the monitoring equipment is taken to the delivery, the infant is randomised into the study by opening the next envelope, and they do indeed require stabilisation.

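### Forty infants give about 87% power for 71 mL/min/kg on a two-sided t-test, not 90%, and the figure is tied to infants randomised although some may not be analysable

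*Protocol article*

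**What the plan says.** The Sample size section gives the variability from the group's own earlier study: "The standard deviation of the minute volume was 71 mL/min/kg". It takes the same value as the target difference and concludes: "Randomisation of 40 infants allows us to detect a difference of 71 mL/min/kg between the two groups with 90% power", at the 5% level. Neither the test nor its sidedness is named there. The Methods section fixes equal allocation: "Infants are allocated to parallel groups in a 1:1 ratio".

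Three other places affect how many of the 40 reach the analysis.

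- **Enrolment.** An infant counts as enrolled if the monitor is taken to the delivery, "the infant is randomised into the study by opening the next envelope, and they do indeed require stabilisation".
- **Exclusion criteria and Recruitment.** Refusal "of consent for the data to be analysed (see later") is an exclusion. Parents are asked for this consent only once the infant has been delivered, hence after randomisation.
- **Background.** Citing an earlier source, the article reports: "Seventy-five percent of infants born at < 34 weeks of gestational age require resuscitation".

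The Abstract says that 40 infants are being recruited. The Statistical analysis section promises intention to treat, looks for any significant difference between the groups, and switches to non-parametric methods if the data are not normal.

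**The concern.** The sample size statement supplies every input that a two-group comparison of means needs, so the stated power can be checked directly. A difference equal to the standard deviation with 20 per arm looks slightly too small a trial for 90% power.

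The statement also attaches the power to infants randomised. Power depends on infants analysed, and the article's own rules let the second number be smaller than the first.

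What is at stake is how a null result would be read. In a single-centre trial of 40 infants, a reader would set a non-significant primary outcome against a claimed type II error of 10%. On a two-sided t-test it is about 13% with no loss at all, and more with any loss.

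**Working it through.** **Inputs**

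- Difference δ = 71 mL/min/kg and SD σ = 71 mL/min/kg (Sample size), so the standardised difference is d = 71/71 = 1.
- 40 infants at 1:1 (Sample size, Methods), so n = 20 per arm.
- Significance level 5% (Sample size). Two-sided is assumed, because the Statistical analysis section looks for any difference.

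**Step 1: reproduce the stated 90%**

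Normal approximation: power = Φ(d√(n/2) − 1.960) = Φ(3.162 − 1.960) = Φ(1.202) = 88.5%.

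Two-sample t-test: noncentral t with 2n − 2 = 38 degrees of freedom and noncentrality d√(n/2) = 3.162. Power = 86.9%.

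One-sided 5% t-test, same inputs: 92.8%.

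The normal approximation comes within 1.5 points of the stated figure and the t-test within about 3 points. Neither two-sided calculation reaches 90%. The one-sided test exceeds it.

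**Step 2: the number needed for 90%**

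Normal approximation: n = 2(1.960 + 1.282)²/d² = 21.01 per arm. That rounds up to 22 per arm, or 44 infants.

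t-test: 22.02 per arm. With 44 infants power is 89.97%, and with 46 it is 91.2%.

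**Step 3: the difference that 40 infants detect with 90% power**

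Solving the two-sided t-test at n = 20 gives d = 1.052. In the protocol's units this is 1.052 × 71 = 74.7, or about 75 mL/min/kg.

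**Step 4: the effect of losing infants after randomisation**

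The article gives no loss rate, so the rows below the first are illustrations (d = 1, 5% two-sided).

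| Analysed (per arm) | Share of 40 lost | t-test | Normal approx. |
|---|---|---|---|
| 40 (20) | none | 86.9% | 88.5% |
| 38 (19) | 5% | 85.1% | 86.9% |
| 36 (18) | 10% | 83.0% | 85.1% |
| 30 (15) | 25% | 75.3% | 78.2% |

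The last row needs two conditions: the 40 are envelopes opened, and the Background figure of 75% needing resuscitation is this trial's rate, so that 0.75 × 40 = 30. Letting each arm's size vary as binomial(20, 0.75) gives an average of 74.6%, so treating the loss as fixed makes little difference.

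**The case against.** **The gap is within planning uncertainty.** With all 40 analysed, the shortfall is 1.5 to 3 points. The standard deviation comes from one earlier study. Had it been 67 instead of 71, d would be 71/67 = 1.06 and 20 per arm would give 90.4% by the t-test. This stands as a comment on size: the stated 90% is optimistic rather than badly wrong. It does not make 90% the right figure for the inputs printed.

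**A one-sided test would meet the claim.** The Sample size section postulates a higher volume in the sustained inflation group and does not state sidedness. One-sided, 40 infants give 92.8%, and 18 per arm already give 90.2%. However, the Statistical analysis section tests for any difference, and the Discussion allows for the standard inflations proving superior. Both favour a two-sided reading.

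**A condensed article need not carry every detail.** A named test or an attrition allowance may be in the full protocol, so their absence here is not a finding. What remains is that the printed statement links 90% power to a count of infants randomised.

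**The stronger reading does not hold.** A reader might put the Enrolment rule and the Background figure together and infer that the protocol implies a 25% loss and hence about 75% power. The documents do not support this. The 75% is a background figure about needing positive pressure ventilation and/or intubation, and it is never offered as this trial's rate. The Enrolment section speaks of stabilisation, which is not defined as the same thing. Infants who do not need it are not enrolled at all, so if the 40 being recruited are enrolled infants, this source of loss is zero.

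**Conclusion.** The point holds in a limited form. On the protocol's own inputs and a two-sided 5% test, 40 analysed infants give 86.9% power by the t-test, or 88.5% by the normal approximation. The type II error is about 13% by the t-test, against the 10% claimed. This rests on the two-sided reading, normal data and equal arms of 20.

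The tie to infants randomised is a second, separate weakness. Refused consent can lower the number analysed below the number randomised. Infants not needing stabilisation can do so too, but only if the 40 counts every envelope opened. How far power falls cannot be settled from the article: 83% at 36 analysed and 75% at 30 are illustrations, not losses that the protocol states.

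Severity is minor to moderate. The stated power needs correcting and the count needs defining, but nothing in the design has to change.

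**What to change.** Replace the power sentence with one that names the count, the test and the sidedness, for example: *Forty infants with a consented, analysable first-minute recording (20 per arm) give 87% power for a difference of 71 mL/min/kg, or 90% power for 75 mL/min/kg, with a two-sided 5% t-test (SD 71 mL/min/kg).* Recruitment would then continue until 40 such recordings are available.

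If the 40 are meant as infants randomised, say so, state the loss expected from refused consent and from infants not needing stabilisation, and quote the power at the number then expected in the analysis.

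The cost is one sentence and a slightly less favourable stated power. The target of 40 analysed infants need not rise, although if the 40 are defined as analysable recordings a few more envelopes may be opened to reach it.

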### Data collection

Demographic and outcome data will be collected from the clinical records and recorded under a unique study number on a password-protected computer. The gestational age, birthweight, sex, exposure to antenatal steroids, presence of chorioamnionitis, mode of delivery, need for mechanical ventilation in the first 48 h after birth, total duration of mechanical ventilation, duration of oxygen therapy, pneumothorax, BPD (oxygen dependency at 28 days after birth), patent ductus arteriosus and the findings on the first cranial ultrasound scan will be recorded for each infant. Traces from the respiratory function monitor will be analysed by the investigators to determine minute volume, ETCO_2_ level and the time to the first active inflation using customised Spectra software (3.0.1.4) (Grove Medical, London, UK).

The order of study events is detailed in the Standard Protocol Items: Recommendations for Interventional Trials (SPIRIT) figure in Fig. 2. A SPIRIT checklist is also provided as an Additional file 1.

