
There have been concerns raised regarding potential adverse effects of sustained inflations, in particular relating to air leak, intraventricular haemorrhage (IVH) and patent ductus arteriosus [22, 23]. Non-significant increases in IVH in infants born at < 28 weeks of gestational age [16] and non-significant increases in pneumothorax in infants born at < 34 weeks of gestational age have been reported in those exposed to sustained inflations [19]. A meta-analysis of four small trials [24], however, showed no significant differences in rates of pneumothorax or of IVH. A subsequent study of prematurely born infants showed a non-significant decrease in pneumothorax with a 15-s sustained inflation compared to ventilation with a self-inflating bag [25]. The peak inspiratory pressures, however, used in the bag-mask ventilation were up to 40 cmH_2_O, whereas those used in the sustained inflation group were 30 cmH_2_O [25]. The meta-analysis [24] also reported that in the sustained inflation group there was a higher proportion of infants who required treatment (medical or surgical) for a patent ductus arteriosus (relative risk = 1.27 [95% confidence interval = 1.05–1.54]). Cerebral blood flow, as assessed by near-infrared spectroscopy, however, was more stable in preterm infants resuscitated with a sustained inflation compared to in those who were resuscitated without a sustained inflation [26–28]. In addition, in prematurely born infants, a 5-s inflation compared to a 2-s inflation was not associated with higher levels of inflammatory cytokines (IL-6, IL-10, IL-1β, and TNF-α) in bronchoalveolar fluid [29].

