### Inclusion criteria

Inclusion criteria are as follows:Infants delivered at < 34 weeks of gestational age.The clinical team present before delivery and trained both in the use of the respiratory function monitor and to deliver sustained inflations.

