### Safety

Reports of related and unexpected serious adverse events will be submitted to the Research Ethics Committee within 15 days of the chief investigator becoming aware of the event. The parents will be informed of any events as soon as possible and be provided with an opportunity to meet with clinical and research team. Although meta-analysis of previous trials has not demonstrated an increased risk, the research team will specifically monitor for incidence of pneumothoraces as a potential identifiable adverse event. The results of any reports or investigations relating to the events will also be communicated to the parents in writing.

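### Cranial findings are recorded from the first ultrasound scan only, so a named potential harm of sustained inflation (IVH) is described incompletely by arm

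*Protocol article*

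**What the plan says.** In the protocol article, Data collection lists what is taken from the clinical records. For the brain it states that "the findings on the first cranial ultrasound scan will be recorded for each infant". The same list includes pneumothorax and patent ductus arteriosus, neither tied to a first examination, and BPD assessed at 28 days after birth.

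The Background reports concern about "potential adverse effects of sustained inflations, in particular relating to air leak, intraventricular haemorrhage (IVH) and patent ductus arteriosus". It cites "Non-significant increases in IVH in infants born at < 28 weeks of gestational age" among those exposed to sustained inflations, and then a meta-analysis of four small trials that "showed no significant differences in rates of pneumothorax or of IVH".

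The Safety section says that "the research team will specifically monitor for incidence of pneumothoraces as a potential identifiable adverse event". Its only other route is general: "Reports of related and unexpected serious adverse events will be submitted to the Research Ethics Committee within 15 days".

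Eligibility is "Infants delivered at < 34 weeks of gestational age", with no lower limit stated, so infants below 28 weeks can be enrolled. IVH is neither the primary outcome (minute volume) nor a secondary outcome (time to first active inflation, and ETCO2).

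**The concern.** The word 'first' is a restriction written into the article. It is not a detail passed over in silence. If a first scan is clear and a later one shows a haemorrhage, the stated rule records the infant as clear. If a haemorrhage seen on the first scan later extends, the rule keeps the earlier grade. Of the three harms the Background names, only the cranial one is limited to a first look.

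At stake is the completeness of a harm count. A trial of 40 infants cannot test for a difference in IVH, so its harm data are useful mainly as full counts by arm that others can read alongside further trials. A first-scan count is a different quantity from the worst finding over a stated period, and a reader could take one for the other.

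**Working it through.** The plan states no figure on this point, so there is none to reproduce. The check is a comparison of sections, followed by an illustration of size.

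**Step 1: how each harm named in the Background is captured.**

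| Harm | Data collection | Safety section |
|---|---|---|
| Air leak (pneumothorax) | Recorded, no limit to a first examination | Specifically monitored |
| Patent ductus arteriosus | Recorded, no limit to a first examination | General route only |
| IVH | First cranial scan only | General route only |

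**Step 2: whether another route closes the gap.** The general route needs a serious adverse event that is judged both related and unexpected. A later haemorrhage judged unrelated, or regarded as expected at this gestation, would not enter it. The route therefore does not yield systematic counts by arm.

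**Step 3: illustrative size.** From the document: N = 40, allocated 1:1. Assumed, because the documents give neither: p, the proportion of infants who ever have IVH, 10% to 30%; and s, the share of those cases visible on the first scan, 50% to 90%.

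- Expected unrecorded cases among 40 = 40 × p × (1 − s)
- Chance that at least one is unrecorded = 1 − [1 − p(1 − s)]^40

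| p | s = 50% | s = 70% | s = 90% |
|---|---|---|---|
| 10% | 2.0 (87%) | 1.2 (70%) | 0.4 (33%) |
| 20% | 4.0 (98.5%) | 2.4 (92%) | 0.8 (55%) |
| 30% | 6.0 (99.8%) | 3.6 (98%) | 1.2 (70%) |

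Each cell gives expected unrecorded cases, with the chance of at least one in brackets. For the middle cell, 40 × 0.20 × 0.30 = 2.4 of 40 × 0.20 = 8 expected cases, and 1 − 0.94^40 = 0.92. The range is 0.4 (40 × 0.10 × 0.10) to 6.0 (40 × 0.30 × 0.50). If every haemorrhage were visible on the first scan (s = 100%), the number would be zero. The table does not count haemorrhages seen at first scan that later extend; those would be recorded at too low a grade.

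**The case against.** The strongest reply is that IVH is not a declared outcome. The scan is one field in a descriptive list, the article promises no IVH comparison, and its Discussion says physiological outcomes were chosen to suit a small sample. This stands, and it limits the point to how fully a harm is described.

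The size also rests on values from outside the documents. They do not say when haemorrhage becomes visible, when first scans are done or that later scans are routine. This stands too: the table shows only what the assumptions imply.

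The Background is more balanced than the IVH signal alone suggests. That signal comes from a comparison with a historical cohort, which the article says to read with caution. The article also cites the null meta-analysis and more stable cerebral blood flow with sustained inflation. That weakens the prior for harm, but it does not explain why IVH alone is limited to a first examination.

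A first scan has merits: it lies closest to the intervention and is least affected by later unblinded care. A worst grade depends on how many scans an infant has, on survival and on transfer. This is a fair trade-off, and the reason to keep both fields.

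Three stronger readings are tempting. A reader might infer that scan timing would differ between arms because the trial is unblinded. Nothing in the article links scan timing to allocation, and it says ongoing care follows unit guidelines. A reader might infer that the data could not be pooled with other trials. The article does not support that; the definition would simply be narrower. A reader might also call the lack of a stated scan age an error. Fig. 2 and the full protocol are not available and may give it.

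**Conclusion.** The point holds as a minor one. As written, the data rule leaves uncounted any haemorrhage that first appears or extends after the first scan, although the article itself names IVH as a potential harm, and no other stated route counts such cases by arm. The conclusion depends on one assumption, that some haemorrhages appear or extend after the first scan and are seen on a scan done in routine care. The number affected cannot be derived from the documents; the 0.4 to 6 of 40 is an illustration over assumed inputs. The primary and secondary results and the sample size are unaffected. Even complete counts would not make an IVH comparison between the arms reliable in a trial of this size.

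**What to change.** In Data collection, keep the first-scan finding and add two items from the clinical record: the infant's age at that scan, and the worst IVH grade on any cranial scan done in routine care up to a fixed, stated age. Report the first-scan finding and the worst grade descriptively by arm, with no significance test, and give the number of infants per arm who had at least one later scan.

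The cost is two extra fields. The record review already runs to at least 28 days for BPD, and no additional scan or change in care is needed. The downside is that later scans may be missing or uneven because of transfer, death or clinical indication. The report should say how many infants this affects in each arm, so that a clear record is not mistaken for a complete one.

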**Fig. 2 Fig2:**
[figure not shown]
SPIRIT figure of trial interventions and timings

### Statistical analysis

Analysis will be conducted on an intention-to-treat basis. The data will be assessed for normality and if found not to have a normal distribution, non-parametric statistics will be used to assess if there are any significant differences in outcomes between the two groups. Analysis will be undertaken using IBM SPSS Statistics for Windows, version 22.

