### Randomisation

The randomisation sequence is generated using a computerised random number generator and concealed in sealed, opaque envelopes. This is done by a person independent of the research team who is not involved in the study.

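### A normality check on the outcome data decides whether the primary comparison is of means or of ranks, so the quantity estimated is not fixed; one pre-specified regression on arm and gestational age would fix it cheaply.

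*Protocol article*

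**What the plan says.** The Statistical analysis section sets an intention-to-treat analysis and then a rule for choosing the test: "The data will be assessed for normality and if found not to have a normal distribution, non-parametric statistics will be used". It does not say how normality is judged or whether it is judged per arm or pooled, and it names neither of the two tests.

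The Sample size section is written in terms of means. It reports that "The standard deviation of the minute volume was 71 mL/min/kg" and that "Randomisation of 40 infants allows us to detect a difference of 71 mL/min/kg", "with 90% power at the 5% significance level". The Methods section gives the allocation: "Infants are allocated to parallel groups in a 1:1 ratio".

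Three other places bear on the remedy. Eligibility covers every gestation below 34 weeks (Inclusion criteria). The Randomisation section says "The randomisation sequence is generated using a computerised random number generator" and describes no stratification. The Data collection list begins "The gestational age, birthweight, sex, exposure to antenatal steroids", so gestational age will be in the data set for every infant.

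**The concern.** The protocol states a rule on this point, so the matter is not simply left to a later document. An analysis plan that followed the rule would inherit it.

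Under one branch the primary result is a difference in mean minute volume, the quantity the trial was sized on. Under the other it is a comparison of ranks, which does not estimate that difference. Which one is reported depends on a check with little information at about 20 infants per arm. The trial is unblinded and the investigators read the traces themselves, so there is good reason to leave no analytic choice open once outcome data exist.

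With 40 infants across a wide gestational range, the arms may also differ in gestation by chance. A fixed model that includes gestational age would settle the estimand and handle the linear part of that imbalance.

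**Working it through.** **Inputs from the protocol.** N = 40, 1:1, so 20 per arm; difference 71 and SD 71 mL/min/kg (standardised effect 1.0); 5% significance; 90% power claimed. Sidedness is not stated and two-sided is assumed.

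**Inputs assumed.** The t-test and Mann-Whitney test as the two branches; Shapiro-Wilk at 5% in each arm, switching if either rejects; the shape of the outcome distribution; the share of outcome variance (R²) explained by gestational age.

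**1. The plan's own figure.**
- Non-centrality = (71/71) × √(20/2) = √10 = 3.162.
- Normal approximation: Φ(3.162 − 1.960) = 88.5%.
- Two-sided t-test, 38 df: 86.9%.

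The claimed 90% is thus met to within 1.5 to 3.1 points. The shortfall is small, but there is no reserve.

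**2. How often the check switches the test (20 per arm).**

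| Assumed data | Trials switched to ranks |
|---|---|
| Normal | about 10% (1 − 0.95² = 9.75%) |
| Gamma, mean 180, SD 71 | 35% |
| Gamma, mean 142, SD 71 | 49% |

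The gamma shapes are (180/71)² = 6.4 and (142/71)² = 4, so skewness (2/√shape) is 0.79 and 1.0. If the second arm is instead a gamma with mean 71 higher and the same SD, it is less skewed and the rates fall to 29% and 41%. With the target difference present, the t-test and Mann-Whitney disagreed on significance in about 5 to 6% of trials.

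**3. Type I error of the two-stage rule.** 0.051 for normal data; 0.050 for lognormal data with sigma 0.6; 0.053 and 0.051 for the two gamma cases (3,000 runs), and about 0.054 in both in a longer run of 40,000. This is close to nominal throughout.

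**4. Gestational imbalance.** The SD of the between-arm difference in mean gestation is √(2/20) = 0.316 SD, so P(|difference| > 0.5 SD) = 2 × [1 − Φ(0.5/0.316)] = 11.4%. If the correlation with minute volume were 0.4 (assumed), an imbalance of 0.5 SD would move the unadjusted estimate by 0.4 × 0.5 × 71 = 14 mL/min/kg, or 20% of the target.

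**5. Power of the adjusted analysis.** Non-centrality = √(10 / [(1 − R²)(1 + 1/36)]), 37 df. The factor 1 + 1/(N − 4) is the price of estimating the covariate effect.

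| Assumed R² | Non-centrality | Power |
|---|---|---|
| 0 | 3.119 | 85.9% |
| 0.10 | 3.288 | 89.3% |
| 0.20 | 3.487 | 92.4% |
| 0.30 | 3.728 | 95.3% |

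Against the unadjusted 86.9%, adjustment gains only if |r| exceeds about 0.17, and it reaches 90% only at |r| of about 0.35 (R² about 0.12). Simulation agrees: 85.8% at r = 0 and 91.0% at r = 0.4, against 91.2% by formula at r = 0.4.

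**6. Power with skewed data and a shift of 71, no covariate.**

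| Data | t-test | Mann-Whitney | Two-stage rule |
|---|---|---|---|
| Gamma, mean 142 | 0.874 | 0.902 | 0.901 |
| Gamma, mean 180 | 0.871 | 0.887 | 0.889 |
| Lognormal, sigma 0.6 | 0.861 | 0.962 | 0.961 |

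**The case against.** The strongest defence is that the rule does no measurable harm to error rates and can help. Type I error stays near 5%, and with skewed data the two-stage rule has more power than a t-test (step 6). This stands. It means the case rests on fixing the estimand, and that a mean-based analysis gives up some power if the data are skewed and gestation is only weakly prognostic.

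Three stronger readings are tempting, and the document supports none of them.

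- A reader might infer that adjusting for gestational age would restore the full 90% power. No correlation between gestation and minute volume is given, the sample size already works per kilogram (which may remove part of the size-related variation), and even R² = 0.10 gives 89.3%.
- A reader might infer that adjustment removes chance imbalance. It corrects only the linear effect of gestation, not antenatal steroids, chorioamnionitis or mode of delivery. Randomisation already makes the unadjusted comparison valid, so an 11.4% chance of imbalance is not evidence of bias.
- A reader might infer that the trial has ruled out covariate adjustment. This is a condensed article, and covariates are commonly left to an analysis plan, which is not shown. Adjustment is offered here as part of the remedy, and its absence is not counted as an error.

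It is also fair to object that a remedy allowing any robust or bootstrap standard error would leave a choice open. In 3,000 null runs with gamma data at n = 40, basic sandwich errors (HC0, normal reference) gave type I error of 0.068, whereas HC3 and ordinary errors gave 0.050. The method must be named.

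**Conclusion.** The point holds as a cheap improvement. The stated rule leaves the primary estimand to the data, at odds with a sample size built on a mean difference of 71 mL/min/kg. The 35 to 50% switching rate depends on the assumed gamma shapes and the assumed Shapiro-Wilk check; with exactly normal data it is about 10%. No material inflation of type I error was found.

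Fixing the analysis settles the estimand whatever the data look like. Including gestational age adds correction of its linear imbalance and possibly some power. The power effect runs from a loss of about 1 point (R² = 0) to a gain of 2.4, 5.5 or 8.4 points (R² = 0.10, 0.20, 0.30), and the document does not allow a choice within that range.

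**What to change.** Before any outcome analysis, remove the normality check as a gate and name one primary analysis: linear regression of minute volume in the first minute (mL/min/kg) on randomised arm and gestational age in weeks, reporting the adjusted mean difference with its 95% confidence interval. Name one standard-error method, for example ordinary or HC3 standard errors with a t reference, and avoid HC0 with a normal reference. Report the rank test as a fixed sensitivity analysis, whatever the distribution looks like.

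The cost is a change of wording and one degree of freedom; no new data are needed. The downside is about 1 point of power if gestation is unrelated to the outcome, and somewhat less power than a rank test if the data are skewed and gestation is only weakly prognostic.
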